## Analysis

Comparisons will be made of the primary endpoints of both intervention groups for all randomized patients who underwent surgery involving the pp-Whipple procedure. Patients will be analysed as randomized applying the ITT principle [18]. In addition, a per-protocol analysis will be performed, including patients who are strictly treated according to the study protocol.

The outcome measures of the primary endpoint will be tested confirmatory applying an analysis of covariance with treatment as factor and age and BMI as continuous covariates.

Secondary endpoints will be analysed in a descriptive manner. Graphically methods will be used by means of box- and scatter- plots. For all continuous secondary endpoints a t-test will be applied, possible differences of categorical secondary endpoints will be analysed using chi-square tests. All p-values will be used as descriptive statistics only without any confirmatory value.

The secondary endpoint Quality of Life (EORTC QLQ-C30, EORTC QLQ PAN26) will be anlysed by an application of analysis of covariance that adjusts for age and EORTC QLQ-C30, EORTC QLQ PAN26 before surgery.

The following procedure will be applied for missing data:

If at least half of the items from the scale have been answered, the missing items are replaced by the average of those items that are not missing (calculated average rounded to the nearest integer). If less than half of the items from the scale have been answered, the scale is set to missing [19].

If it is evident that missing items or missing scales are related to a worsening in physical functioning, the missing values are replaced by the worst value measured in the respective intervention group at the respective time point.

The average EORTC QLQ-C30, EORTC QLQ PAN26 score can be calculated, if at least one measurement at day 30 (±10days), 90 (±10 days), 180 (±10 days), 1 year (± 1 month), 1,5 years (± 1 month), 2 years (± 1 month), 2,5 years (± 1 month) or 3 years (± 1 month) after surgery is available; if no measurement of the EORTC QLQ-C30 or EORTC QLQ PAN26 after surgery is available, the secondary endpoint is missing and the patient is therefore not included into the analysis.

All statistical analyses will be performed using SAS^® ^software, Version 9.1 (or higher) of the SAS System for Unix (SAS Institute Inc., Cary, NC, USA).

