### Number of patients needed

The sample size calculation is based on a two sided t-test for differences with respect to the primary endpoint. The data evaluation and comparison of seven patients operated on with the LVSS versus seven patients operated on with the conventional dissection technique showed a reduction of operating time of 40 minutes in the LVSS group. An evaluation of all pp-Whipple operations in 2010 (138 operations) showed a mean operating time of 300 min with a standard deviation of 66 minutes. If the difference in operating time is 40 minutes, there will be an 80% (1-β) chance that a trial involving 88 patients (44 per group) could detect a significant difference at an alpha level of 5%s (SAS 9.1 proc power). To compensate possible drop outs 14 patients (15%) more will be randomized. Therefore 102 patients (51 per group) will be included (Figure 1).

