### Randomization and procedures for minimizing bias

#### Minimizing systemic bias

To achieve comparable groups for known and unknown risk factors randomization will be performed as unstratified block randomization with random block sizes in a 1:1 allocation ratio. Allocation to treatment group will be carried out by the randomization software RITA^® ^[17]. Randomization numbers that become vacant by withdrawal will be reused.

102 patients will be recruited according to the sample size calculation. Randomization will be performed independently by a study nurse of the Clinical Study Center Surgery (KSC) to the conventional group or to the LVSS group. Randomization will be carried out after patient has signed the informed consent and will be documented in the case report file of every patient. Intervention will be scheduled 1-3 days after inclusion depending on the earliest operation appointment possible.

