#### Minimizing treatment bias

A standardized operation technique will be used in both groups. The same LigaSure™ device will be used in the LVSS group. The physician responsible needs to have experience of at least 100 pp-Whipple procedures and will be trained and updated every three months to guarantee comparable treatment of patients.

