### Safety aspects

#### Specification of safety variables

##### Training for surgeons

In each operation there will be a surgeon (senior surgeon) who has experience of at least 100 pp-Whipple procedures. The operation will be carried out as a standard procedure; the LigaSure™ device has been used in the department for several years already.

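### Neither the primary ANCOVA nor the randomization accounts for the operating surgeon; adding the surgeon planned before allocation is a cheap gain in precision and protection

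*Protocol article*

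**What the plan says.** The Analysis section states the confirmatory model outright: an "analysis of covariance with treatment as factor and age and BMI as continuous covariates". Under Minimizing systemic bias, allocation is by "unstratified block randomization with random block sizes in a 1:1 allocation ratio". Surgeon is therefore not a covariate, a random effect or a stratification factor.

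The surgeon is addressed by conduct rules instead. Minimizing treatment bias asks for a standardized technique and three-monthly training, and says "The physician responsible needs to have experience of at least 100 pp-Whipple procedures". Training for surgeons says "In each operation there will be a surgeon (senior surgeon) who has experience of at least 100 pp-Whipple procedures". The withdrawal criteria mention separately the surgeon who performs the dissection. The article does not say whether these descriptions always mean the same person.

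The primary endpoint is the time from skin incision to skin closure. The sample size rests on a "two sided t-test for differences with respect to the primary endpoint", with a difference of 40 min and an SD of 66 min taken from all 138 pp-Whipple operations in 2010.

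**The concern.** Skin-to-skin time covers the dissection, where the two techniques differ, and also the reconstruction with its three anastomoses, where operator speed can matter whatever the arm. The article recognises the operator as something to control, since its experience threshold stands under the heading on treatment bias, but it does not carry that factor into the only confirmatory test.

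Two separate things follow. First, variation between surgeons that could be explained stays in the error term, so precision is given away. Second, if faster surgeons did more of the operations in one arm, the difference in surgeon mix would pass straight into the treatment estimate. The article does not state that the surgeon is fixed before allocation or that the result is withheld until surgery. It says only that patients are randomized pre-operatively after consent, that surgery follows 1-3 days after inclusion, and that physicians cannot be blinded.

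**Working it through.** **Inputs from the article:** difference 40 min, SD 66 min, two-sided alpha 5%, 44 per arm (Number of patients needed). **Assumed, because the article gives no figure:** the surgeon share of variance, rho; the number of surgeons; and any difference in surgeon mix between arms.

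**1. The plan's own figure.** SE = 66 × sqrt(2/44) = 14.1 min. The two-sample t-test (noncentral t) needs 43.7, so 44 per arm, with power 80.3% at 44. The stated 88 reproduces, and 88 × 1.15 gives about 101, or 102 rounded up to equal arms.

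**2. Precision forgone.** Residual SD = 66 × sqrt(1 − rho), then t-test power for 40 min with 44 per arm:

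| rho (assumed) | Residual SD, min | Power at 44 per arm | n per arm for 80% |
|---|---|---|---|
| 0 | 66.0 | 80.3% | 44 |
| 5% | 64.3 | 82.2% | 42 |
| 10% | 62.6 | 84.2% | 40 |
| 20% | 59.0 | 88.2% | 36 |
| 30% | 55.2 | 91.9% | 31 |

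These powers are upper limits. They assume a balanced surgeon mix, ignore the degrees of freedom spent on surgeon, and start from 66 min although age and BMI may already remove some variance. In a simulation with six assumed surgeons as a fixed factor (3,000 runs per setting), power went from 81.7% to 82.5%, 82.0% to 85.7% and 82.0% to 90.5% for rho of 10%, 20% and 30%.

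**3. Validity when assignment is unrelated to arm.** In the same simulation, the model without surgeon showed no bias (mean estimate within 0.2 min of zero under the null) and type I error of 4.6-5.7%.

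**4. What a differing surgeon mix would do.** Simple form: bias = difference in mix × difference in speed. With an assumed 10 points and 40 min, bias = 0.10 × 40 = 4 min, which is 4/14.1 = 0.28 SE, and type I error is about 5.9% (normal approximation). In the simulation, with the faster half of the surgeons used more often in the LVSS arm and rho of 10/20/30%:

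- 20-point difference: bias 6/8/10 min, type I error 7/8/12%.
- 40-point difference: bias 12/17/20 min, type I error 14/24/32%.

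With the surgeon who actually operated in the model, bias was at most 0.6 min and type I error 4.3-5.5%.

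**The case against.** The strongest reply is that nothing stated is wrong. Under 1:1 randomization, an ANCOVA that omits a prognostic covariate is a valid test, and step 3 bears this out. The planning SD comes from every operation of a full year at the same centre, so whatever surgeons contribute is already paid for in the 44 per arm. This stands: planned power is not lost, and adjustment offers a gain above target.

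A reader might infer more, namely that surgeon is a main driver of operating time and that operators are chosen after an open allocation. The documents do not support either as fact. They give no between-surgeon variation, and the 100-procedure threshold, training and standardized technique are meant to keep it small. On blinding, the article says only that it is impossible because the techniques differ during the operation, not that the team learns the arm beforehand. The 1-3 days run from inclusion, not from randomization, and a study nurse randomizes independently. Release of the allocation and theatre rostering are details that a condensed article may leave to the full protocol. The larger biases in step 4 need selective imbalances for which there is no evidence.

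It is also fair to object that adjusting for the actual surgeon conditions on something that may be settled after randomization, while adjusting for the planned surgeon does not undo a later swap. The fix has to deal with both.

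A surgeon-adjusted sensitivity analysis could be in the statistical analysis plan, which is not shown. That does not remove the point, because the article fixes the confirmatory model itself.

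**Conclusion.** The point holds as a cheap improvement. Surgeon is in neither the randomization nor the confirmatory model of a skin-to-skin time endpoint, although the article treats surgeon experience as a possible source of treatment bias. If surgeon assignment is unrelated to arm, and the 2010 surgeon mix resembles that of the trial, the test is valid and its 80% power is met. The forgone gain is then about 2 to 12 power points at most, for an assumed surgeon share of 5-30%. If the surgeon mix does differ by arm, the unadjusted estimate is exposed. The amount depends wholly on assumptions, from 4 min in a mild example to about 20 min in an extreme one, against a target of 40 min. The article does not exclude such a difference, but gives no sign that it is expected.

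**What to change.** - Record the planned responsible surgeon, and the planned dissecting surgeon if this is someone else, in the CRF before the randomization software releases the allocation. Planned surgeon is then a true baseline variable.
- State which of the two enters the model, and add that planned surgeon to the primary ANCOVA beside treatment, age and BMI. Use a random intercept, or a fixed factor with low-volume surgeons pooled by a prespecified caseload cut-off. If only a few surgeons take part, a random intercept may be poorly estimated and the fixed factor is the safer choice.
- Record the surgeon who actually operated, and report changes from the planned surgeon by arm. Adjustment for the planned surgeon does not correct later swaps, so this table is what shows whether any occurred selectively.
- Keep the age/BMI-only model as a sensitivity analysis.

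The cost is one or two CRF fields, one model term and a few degrees of freedom. The sample size of 102 does not change.

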**Figure 1 F1:**
[figure not shown]
**Flowchart according to CONSORT**.

A minimum time saving of 40 minutes would be needed to change the manner of surgical preparation towards the use of the LigaSure™ because of the high costs of this device. A basic configuration for the use of the LigaSure™ device costs nearly € 30.000, additionally € 260 per patient are the costs for the single use device itself. The pilot trial with 14 patients by Gehrig et al. showed a cost reduction of nearly € 800 per patient for a operative time saving of 40 minutes (€ 500 for 30 minutes). Therefore we believe a time saving of at least 40 min would be needed to convince surgeons and hospital managers to consider the purchase and use of this equipment on a rugulary basis.

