#### Secondary endpoints

• Perioperative complications:

○ Intraoperative Bleeding

○ Perforation of hollow organs (stomach, small intestine, colon, gallbladder/biliary tract)

○ Lesion in parenchymatous abdominal viscus (liver, spleen, pancreas)

• Postoperative complications:

○ Secondary bleeding/hematoma

○ Wound infection

○ Gastroparesis

○ Postoperative pancreatic fistula (POPF)

○ Intraabdominal abscess

○ Anastomotic leakage of the choledochojejunostomy

○ Anastomotic leakage of the gastrojejunostomy

• Re-intervention (operational/interventional)

• Intraoperative blood loss

• Hospital stay

• Re-hospitalization-rate (30 days postoperative)

• Duration of anesthesia

• Intraoperative material consumption

• Material costs, calculated by the material consumption

• Overall costs of the operation, calculated by the indirect and direct costs during the hospital stay and the costs accumulated 30 days postoperatively

• Local recurrence of disease

• Quality of life analysed in questionnaires (EORTC QLQ-C30, EORTC QLQ PAN26, special questionnaire of the European Pancreas Center, University of Heidelberg)

• Mortality rate

Definitions of secondary endpoints are shown in Table 2.

**Table 2 T2:** Definition of secondary endpoints

Perioperative complications	Complication	Definition
Bleeding	Severe intraoperative bleeding	Mentioned in operation report

Perforation of hollow organs	Perforation of stomach, small intestine, colon or biliary tract/gallbladder	Mentioned in operation report

Lesion in parenchymatous abdominal viscus	Lesion in liver, spleen, pancreas	Mentioned in operation report

Postoperative complications	Complication	Definition

Secondary bleeding/hematoma	postoperative bleeding	Need for more than 2 units of red blood cells within 24 hours after surgery OR Need of surgical treatment (mentioned in re-operation report)
	
	Hemtoma	Radiological (ultrasound, CT) findings positive for reoperation or reopening of the wound

wound infection		Deep and/or superficial according to CDC definition [20]

Gastroparesis	delayed gastric emptying (DGE)	Consensus definition of delayed gastric emptying after pancreatic surgery of the International Study Group of Pancreatic Surgery (ISGPS) [21]

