pp-Whipple specific complications	postoperative pancreatic fistula (POPF)	Drain output of any measurable volume of fluid on or after postoperative day 3 with an amylase content greater than 3 times the serum amylase activity. Three different grades of POPF (grades A, B, C) are defined according to the clinical impact on the patient's hospital course [22]
	
	Intraabdominal abscess	Intraabdominal collection of purulent or infected fluids (positiv bacterial culture) requiring radiological (puncture or drainage of purulent fluid) or surgical intervention (re-operation)
	
	anastomotic leakage of choledochojejunostomy	Bilirubin-rich (more than 5000 units) drainage fluid of more than 50 ml per day on or after the 10th postoperative day OR Mentioned in re-operation report
	
	anastomotic leakage of gastrojejunostomy	Radiological findings correlating to gastrojejunostomy insufficiency (e.g. CT with contrast medium withdrawal) OR Mentioned in re-operation report

Further secondary endpoints		Definition

Re-intervention	operational	Reoperation due to any cause

	interventional	Interventional haemostasis or drainages due to any cause

Intraoperative blood loss		Mentioned in operation report

Hospital stay		Time of admission to discharge

Re-hospitalization-rate		Re- hospilization within 30 days after surgery due to any cause

Duration of anesthesia		Mentioned in anesthesia report

Intraoperative material consumption		All materials, which are necessary for surgery

Material costs		Costs, which occurs due to the material consumption during the surgery

Overall costs		Costs include expenditure for personnel and use of operating room as well as for material consumption

Local recurrence of disease		Radiological (ultrasound, CT) findings positive for recurrence of disease

Quality of life		EORTC QLQ-C30, EORTC QLQ PAN26 and special questionnaire of the European Pancreas Center Heidelberg on day 30 (±10days), 90 (±10 days), 180 (±10 days), 1 year (± 1 month), 1,5 years (± 1 month), 2 years (± 1 month), 2,5 years (± 1 month) and 3 years (± 1 month)

Mortality rate		Death to any course until year 3 after operation

Assessment:

1. Perioperative complications of the pp-Whipple procedure will be recorded on the day of operation by an independent study nurse.

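### Operating time is adjusted for age and BMI, but overall costs, which contain operating-room use, get an unadjusted t-test: a small, avoidable loss of precision and coherence

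*Protocol article*

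**What the plan says.** The Analysis section of the protocol article names three methods for continuous endpoints.

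- Operating time, the primary endpoint: "analysis of covariance with treatment as factor and age and BMI as continuous covariates".
- Secondary endpoints in general: "For all continuous secondary endpoints a t-test will be applied". No covariates are named, and the section adds: "All p-values will be used as descriptive statistics only without any confirmatory value".
- EORTC quality-of-life scores: "application of analysis of covariance that adjusts for age and EORTC QLQ-C30, EORTC QLQ PAN26 before surgery". BMI is not in this model.

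The secondary endpoint list includes duration of anesthesia, material costs and overall costs. Table 2 defines overall costs thus: "Costs include expenditure for personnel and use of operating room as well as for material consumption". The list itself describes them as "calculated by the indirect and direct costs during the hospital stay and the costs accumulated 30 days postoperatively". Material costs are defined separately: "Costs, which occurs due to the material consumption during the surgery". Table 2 takes duration of anesthesia from the anesthesia report, with no start or end point.

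Under Number of patients needed, in the text after Figure 1, time and money are linked: the pilot comparison "showed a cost reduction of nearly € 800 per patient for a operative time saving of 40 minutes". The same sentence gives €500 for 30 minutes. Randomization is unstratified, so neither age nor BMI is balanced by design.

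**The concern.** By putting age and BMI in the primary model, the plan treats them as likely predictors of operating time. Overall costs contain a part that grows with operating time, so age and BMI should predict that part too. Yet one result is estimated with the covariates and the other without.

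If one arm happens to have heavier or older patients, the linear effect of that imbalance is taken out of the time difference and left in the cost difference. The two results will be read side by side, because the protocol argues for the device by converting minutes into euros. They could then differ somewhat for a reason that has nothing to do with the device. The unadjusted interval is also a little wider than the planned data require.

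This is a rule the protocol states for all continuous secondary endpoints, not a gap left to the analysis plan. A plan that followed it would carry the mismatch forward.

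A smaller instance concerns the centre's own questionnaire. It belongs to the quality-of-life endpoint, and Table 1 schedules quality of life at screening, but the baseline-adjusted model names only the two EORTC instruments. If that questionnaire yields a continuous score, the t-test rule applies to it and its pre-surgery value goes unused.

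**Working it through.** **Inputs from the protocol.** Standard deviation of operating time 66 min; target difference 40 min; 44 per group before and 51 per group after the dropout allowance; €800 per 40 min and €500 per 30 min.

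**Assumptions, not in the protocol.** Correlation r between operating time and the covariate (or the best linear combination of age and BMI) of 0.2 to 0.4; conversion of minutes to euros at a constant rate.

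**1. The plan's own figure.** A two-sided t-test at 5% with difference 40 and SD 66 has exact power 0.793 at 43 per group and 0.803 at 44. The stated 44 per group reproduces, so 66 min is a sound base.

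**2. Standard error without adjustment.** At 51 per group, sqrt(2/51) = 0.198, so the SE of the time difference is 66 × 0.198 = 13.07 min.

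**3. Standard error with adjustment.** The ratio is sqrt(1 − r²).

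| r | SE ratio | Adjusted SE (min) | Reduction |
|---|---|---|---|
| 0.2 | 0.980 | 12.81 | 2% |
| 0.3 | 0.954 | 12.47 | 5% |
| 0.4 | 0.917 | 11.98 | 8% |

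**4. Shift left in an unadjusted comparison.** The chance difference in a standardized covariate has SE 0.198. An imbalance of one SE shifts the time component by 0.198 × r × 66 min.

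- r = 0.2: 2.6 min
- r = 0.4: 5.2 min

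This is r times the SE in step 2, that is, 0.2 to 0.4 of one standard error. An imbalance of two SE, exceeded in about 5% of trials, doubles it to 5.2 to 10.5 min.

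**5. In euros.** The rates are 800/40 = €20 and 500/30 = €16.7 per minute.

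- One SE, lowest case: 2.61 × 16.7 = €44
- One SE, highest case: 5.23 × 20 = €105

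The protocol gives €260 per patient for the single-use device and nearly €800 for the 40-minute saving.

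**6. Sensitivity.** At 44 per group the unadjusted SE is 66 × sqrt(2/44) = 14.07 min, and the one-SE shift is 2.8 min (r = 0.2) to 5.6 min (r = 0.4). Over a wider assumed share of explained variance, 0.02 to 0.30, the shift has a standard deviation of 2.0 to 7.7 min, or €33 to €154.

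**7. Validity of the t-test.** In 40,000 simulated trials of 44 per group, the unadjusted test rejected a true null in 0.049 of trials when the covariate explained 10% of the variance and in 0.050 when it explained 30%, against a nominal 0.05.

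**8. Special questionnaire.** If a continuous score exists and its baseline correlates 0.5 with follow-up (assumed), the ratio is sqrt(1 − 0.25) = 0.866, a reduction of about 13%.

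**The case against.** The best defence is that nothing here is wrong. Under 1:1 randomization the t-test is unbiased and keeps its error rate. Chance imbalance is ordinary sampling error already covered by its interval, and the shifts above are a fraction of one standard error. The endpoints are descriptive and no decision rule hangs on them. Covariates already differ between endpoints in this plan, and the analysis plan, which is not shown, may add supportive adjusted estimates. All of this stands and limits the point to an optional one. It does not remove it, because the stated rule leaves a free gain unused.

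Several stronger readings are tempting but not supported.

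- A reader might infer that the cost comparison is biased or has inflated error. Randomization and the simulation say otherwise.
- A reader might infer that the adoption case would be distorted. The protocol ties adoption to a saving of at least 40 minutes, which is the primary endpoint and is adjusted.
- A reader might infer that duration of anesthesia certainly contains skin-to-skin time. That is the ordinary reading, but Table 2 gives no start or end and Table 1 describes the item as pre- and postoperative anesthesia time, which can be read as excluding the operation.
- A reader might infer that all cost endpoints are affected. Material costs depend on materials used, not on minutes.
- A reader might take the euro figures as the shift in total cost. Overall costs also cover the hospital stay and 30 days after surgery, and the operating-room share is not given. The figures describe the time component only.
- A reader might infer that the special questionnaire is mishandled. The protocol does not say that it produces a continuous score.

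**Conclusion.** The point holds as a low-severity matter of efficiency and coherence. The protocol adjusts the time result and, by a stated rule, leaves unadjusted a cost result that partly depends on time. For assumed correlations of 0.2 to 0.4, the cost is a few percent of the standard error of the time component, and a typical discrepancy between the two results that is small beside the 40-minute target. The size rests on those correlations, on the planning SD, and on the pilot's conversion rates. If age and BMI barely predict operating time, the loss is close to nil. The planned test remains valid and the primary analysis is untouched.

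**What to change.** In the Analysis section, next to the t-test rule, state that for overall costs the treatment difference and its 95% interval will be reported from the primary model (treatment, age, BMI), in place of or alongside the t-test. Apply the same to duration of anesthesia if its definition is clarified to include the operation. If the special questionnaire yields a continuous score, adjust it for its pre-surgery value, as for the EORTC scores. There is no need to extend the model to endpoints such as material consumption.

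The cost is one sentence of wording and two model degrees of freedom. Age and BMI are already in the primary model, and quality of life is already scheduled before surgery, so no new data or patients are needed. The sentence should be fixed before the data are seen; adjustment chosen after an imbalance appears would look data-driven.

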**Methods/Design:**

A single-center, randomized, single-blinded, controlled superiority trial to compare two different techniques for dissection in a pp-Whipple procedure. 102 patients will be included and randomized pre-operatively. All patients aged 18 years or older scheduled for primary elective pp-Whipple procedure who signed the informed consent will be included. The primary endpoint is the operating time of the randomized technique. Control Intervention: Conventional dissection technique; experimental intervention: LigaSureTM dissection technique. Duration of study: Approximately 15 months; follow up time: 3 years. The trial is registered at German ClinicalTrials Register (DRKS00000166).

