### Eligibility

#### Inclusion criteria

• Clinical suspicion of a cancerous tumour on the head of the pancreas, relied on imaging and laboratory values

• Aged 18 years or older

• Patients scheduled for primary pp-Whipple procedure

• Informed consent

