2. Postoperative complications of the pp-Whipple procedure will be recorded in patients' discharge data and on visit 1 (30 days after operation) after a standardized telephone interview by a study nurse. A confirmation by the patient's family physician will be requested following any abnormality reported by the patient. The following standard aftercare takes place initially twice quarterly (visit 2, 3 months after operation; visit 3, 6 months after operation) then half-yearly for two years (visit 4, 12 months after operation; visit 5, 18 months after operation; visit 6, 24 months after operation; visit 7, 30 months after operation and visit 8, 36 months after operation) with a clinical examination, imaging (ultrasound, CT, MRT), general and standardized questionnaires (EORTC-QLQ-C30, EORTC-QLQ-PAN26 and a special questionnaire from the European Pancreas Center) and laboratory value control in the European Pancreas Center at the surgical department.

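### Three-year mortality and local recurrence fall to a chi-square test, which cannot handle patients lost before 36 months

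*Protocol article*

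**What the plan says.** The Analysis section of the protocol article gives three methods for secondary endpoints:

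- Continuous endpoints: "For all continuous secondary endpoints a t-test will be applied".
- Categorical endpoints: "possible differences of categorical secondary endpoints will be analysed using chi-square tests".
- Quality of life: analysis of covariance.

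Table 2 defines the mortality rate as "Death to any course until year 3 after operation". It defines local recurrence as radiological "findings positive for recurrence of disease", with no time point. The abstract gives "follow up time: 3 years", and the visit schedule under Secondary endpoints ends with "visit 7, 30 months after operation and visit 8, 36 months after operation".

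The missing-data rules in the Analysis section concern questionnaire items and scales only. The section on patient numbers expects drop-outs and adds 14 patients for them. On the status of the secondary tests, the Analysis section says: "All p-values will be used as descriptive statistics only without any confirmatory value".

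**The concern.** Death by year 3 and recurrence are yes/no outcomes, so under the stated rules they go to chi-square. The article does not name them beside that test; they arrive there because nothing else listed fits. The test needs a known status at one fixed time for every patient. Over three years some patients will be lost, and the article gives no censoring rule for them.

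Eligibility is "Clinical suspicion of a cancerous tumour on the head of the pancreas", so many deaths within three years are plausible, and some will come before any recurrence is seen. Table 1 schedules recurrence assessment only from visit 2, at 3 months, so a patient who dies earlier has no planned assessment.

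At stake is whether the long-term rates that the trial reports can be trusted, and, if loss is unequal between the arms, whether the comparison can be.

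**Working it through.** **The plan's own figure.** The documents give no expected rate for mortality or recurrence. Their only sample-size figure concerns operating time: 40 minutes difference, SD 66, two-sided 5%, 80% power, 44 per group. An exact t-test calculation gives power 0.793 at 43 and 0.803 at 44 per group, so 44 is reproduced. Then 88 × 1.15 = 101.2, rounded up to an even 102. This point affects none of it.

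**Assumed inputs.** True three-year mortality D = 70%; probability L of loss by year 3 in the absence of death = 20%, with 10%, 15% and 30% as variants; constant hazards; loss independent of death. The 15% drop-out allowance belongs to the operating-time calculation and is not an estimate of three-year loss.

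**Mortality, formulas.**
- Death hazard l = −ln(1−D)/3; loss hazard g = −ln(1−L)/3, per year.
- Deaths observed: s = l/(l+g) × [1 − (1−D)(1−L)].
- Alive with full follow-up: c = (1−D)(1−L).
- Lost counted as alive: rate = s. Lost dropped: rate = s/(s+c).

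**Mortality, D = 70%, L = 20%.** l = 0.4013 and g = 0.0744. So s = 0.4013/0.4757 × (1 − 0.24) = 0.641, and c = 0.24. Dropping the lost gives 0.641/0.881 = 0.728. About 12% of patients (1 − 0.641 − 0.24) are actually lost before death.

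| Loss L | Lost = alive | Lost dropped | True |
|---|---|---|---|
| 10% | 67.1% | 71.3% | 70% |
| 15% | 65.6% | 72.0% | 70% |
| 20% | 64.1% | 72.8% | 70% |
| 30% | 60.9% | 74.4% | 70% |

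With 15% loss and true mortality of 40% or 60%, the two conventions give 37.2% or 42.2%, and 56.1% or 62.2%.

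**Unequal loss, no true difference.** With L = 10% in one arm and 30% in the other, the 10% and 30% rows give 67.1% versus 60.9% (lost = alive), a spurious 6.2 points. Dropping the lost gives 71.3% versus 74.4%, a spurious 3.1 points the other way.

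**Type I error.** Simulation with 51 per arm, 60% mortality in both arms, 10,000 runs:

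| Loss by arm | Chi-square, lost = alive | Chi-square, lost dropped | Log-rank |
|---|---|---|---|
| 15% / 15% | 5.6% | 4.8% | 5.2% |
| 10% / 30% | 9.7% | 6.5% | 5.1% |
| 5% / 25% | 10.2% | 6.5% | 5.0% |

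**Recurrence, effect of loss.** Assume recurrence and death hazards of 0.02 per month each. Without loss, the 36-month incidence is 0.02/0.04 × (1 − e^(−1.44)) = 38.2%. With 20% loss, g = −ln(0.8)/36 = 0.0062 and the total hazard is 0.0462. Observed recurrence is 0.02/0.0462 × (1 − 0.1895) = 35.1%. Deaths without recurrence are also 35.1%, and 18.95% complete follow-up event-free. Dropping the lost gives 0.351/(0.351 + 0.351 + 0.1895) = 39.4%. The pattern is the same as for mortality, on a smaller scale.

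**Recurrence, effect of death.** Keep the recurrence hazard at 0.02 in both arms, set death hazards at 0.02 and 0.035 per month, and assume no loss. Crude recurrence is 38.2% versus 0.02/0.055 × (1 − e^(−1.98)) = 31.3%.

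**The case against.** The strongest reply is that little depends on these tests. The endpoints are secondary, their p-values are declared non-confirmatory, and the chi-square sentence is a generic line. The article also refers to a prespecified analysis plan, not shown, where endpoint-specific methods may sit. That lowers the weight of the point. It does not remove it, because the article itself states a test and the distortion affects the reported rate as well as the p-value.

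A reader might infer more than the documents support:

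- **That the mortality comparison is biased in any case.** It is not. With complete follow-up, chi-square at year 3 is valid. With equal, non-informative loss, type I error stays near nominal. Nothing shows that loss will be unequal: patients are blinded and aftercare is the same in both arms. One possible route is that the unblinded surgeon may withdraw a patient, with bleeding given as an example. Even the 6.2-point artefact is below the standard error of the difference, about 9.5 points at 51 per arm.
- **That 38% versus 31% shows a wrong result for recurrence.** With full follow-up these figures are the competing-risk cumulative incidence, which a correct analysis would also report. They show only that crude recurrence cannot be read as an effect on recurrence when deaths differ. The documents give no ground for expecting such a difference.
- **That patients with benign histology bias the comparison.** Randomisation balances them on average; they lower the rate in both arms.
- **That a survival analysis would gain much power.** With equal 15% loss and an assumed hazard ratio of 0.6, power is 41–47% for chi-square and 43–49% for log-rank.

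**Conclusion.** The point holds on censoring. As the article stands, the long-term rates will be too low or too high, depending on a convention that it does not fix. Under 70% mortality and 20% loss the reported rate is 64% or 73%; with 15% loss it is 66% or 72%. Bias in the comparison is conditional: it needs unequal or informative loss, and about 6 points at 10% versus 30% loss illustrates its size. All mortality, loss and recurrence rates here are assumptions.

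The weight is modest. The confirmatory analysis of operating time is unaffected. The documents do not support a claim that the stated test reverses the recurrence result or undermines the trial's main conclusion.

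**What to change.** Amend the secondary-endpoint paragraph of the Analysis section, before the data are analysed, to say:

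- **Mortality:** Kaplan-Meier estimates by arm, log-rank test, and a Cox hazard ratio with 95% confidence interval, censoring at last contact.
- **Local recurrence:** cumulative incidence (Aalen-Johansen) with death as a competing event and censoring at last contact, plus a cause-specific hazard ratio.
- **Population:** as randomised, with histologically confirmed malignancy as a supportive subset only.
- **30-day binary outcomes:** chi-square, as now.

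The cost is small but not only wording. The article does not say that dates of death, first positive imaging and last contact are recorded, so the CRF must be checked and, if needed, extended. Visits 2 to 8 are 3 to 6 months apart, so recurrence timing will be known only to the visit interval, and the report should say so. P-values remain descriptive.
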